**Treatment of investigational equipment**

1) No change: When an adverse event occurs, but there is no change in the conditions for conducting investigational device treatment.

2) Discontinuation: When the clinical trial device is discontinued due to the occurrence of adverse events

3) Weight loss: When the current intensity or duration of the investigational device is reduced due to the occurrence of adverse events.

4) Pause: When the operation of the investigational device is temporarily suspended due to the occurrence of an adverse event.

5) Enhancement: When the current intensity of the investigational device is enhanced or the duration is extended due to the occurrence of adverse events.

6) Not applicable: When an adverse event occurs before the start of clinical trial equipment or after the end of the clinical trial period

**Outcome**

1) Recovery: When the adverse event recovers or disappears to the state before the onset

2) Recovered but with sequelae: When the adverse event has recovered but the effects of the adverse event remain as sequelae

3) Death: When the adverse event that occurs is the direct cause of death

4) Relief: Adverse events continue, but symptoms tend to improve

5) Unrecovered: If the adverse event continues (symptoms do not tend to improve)

6) Unknown: When the subject cannot be tracked

**Definition of serious adverse events**

Serious adverse events shall fall under any of the following:

1) What leads to death (death)

2) Life-threatening (risk of death)

3) Items that require hospitalization or extension of hospitalization period

4) Permanent or significant disability / dysfunction

5) Those that cause birth defects

6) Other serious things according to the above

“Hospitalization” for the reasons described below is not considered a serious adverse event.

・ Includes re-examination, hospitalization for follow-up or extension of hospitalization period, and hospitalization (scheduled surgery, examination, etc.) for the sole purpose of performing treatment or examination scheduled before the start of the clinical trial during the clinical trial. No (however, new occurrences during the hospitalization are treated as adverse events).

・ Hospitalization for elective treatment for existing pathological conditions unrelated to the target disease of this study.

・ Hospitalization for social reasons and temporary rest of the caregiver without deterioration of general condition.

The subject of the report was all serious adverse events that occurred from the start of screening to the end (discontinuation) of the study, or events that may occur, and suspected relevance to the study equipment after the end (discontinuation) of the study. It is considered a serious adverse event.

**Procedures for reporting serious adverse events, etc.**

If an adverse event occurs and the investigator, etc. determines that it is serious, the adverse event information will be handled according to the following procedure.

1) Report from the investigator to the head of each medical institution

If the investigator finds that death or other serious adverse events have occurred or may occur due to a malfunction of the investigational equipment during the clinical trial period after the investigational equipment is conducted, the investigator immediately conducts each procedure. Report the content in writing to the head of the medical institution. When reporting, identify whether serious adverse events are unpredictable.

In addition, the investigator should describe the details of the event in the "Report on Serious Adverse Events and Malfunctions" (Unified Form 14) and "Form for Detailed Medical Description" as soon as possible, and the implementing medical institution. Report to the head of.

2) Report from the investigator to the clinical trial coordinating doctor and the sponsor of the clinical trial equipment

If the investigator finds that death or other serious adverse events have occurred or may occur due to a malfunction of the investigational equipment during the clinical trial period after the investigational equipment is conducted, the investigator immediately adjusts the clinical trial. Report the details to the doctor and the provider of the investigational device.

In addition, the investigator should describe the details of the event in the "Report on Serious Adverse Events and Defects" (common to Unified Form 14_ and Medical Details_Form 12_14_19) as soon as possible, and conduct the clinical trial. Report to the coordinating physician.

3) Consultation between the investigator and the investigator

The investigator shall consult with the investigator as necessary and report his / her opinion as the investigator (including the need to report to the Minister of Health, Labor and Welfare) to the investigation coordinating committee.

In addition, if the efficacy and safety evaluation committee is consulted regarding the judgment of the investigator, the opinions of the efficacy and safety evaluation committee will be followed.

4) Report to the Minister of Health, Labor and Welfare

If it is determined that the adverse event or defect is to be reported as stipulated in the Pharmaceuticals and Medical Devices Act, the clinical trial coordinating physician will prepare a "Medical Device Malfunction / Infectious Disease Case Report" (Attachment Form No. 8) and evaluate the efficacy and safety. Report to the committee and PMDA.

For the detailed procedure, follow the "Procedure Manual for Handling Safety Information (tentative name)".

5) Report to the director of the implementing medical institution

When a report is made to the Minister of Health, Labor and Welfare, the investigator shall obtain the "Medical Device Malfunction / Infectious Disease Case Report" (Attachment Form No. 8) obtained from the clinical trial coordinating doctor and, if necessary, "for medical details". Report the contents of the "Form" to the director of the implementing medical institution as soon as possible.

6) Response when additional information is obtained

When additional information about the event is obtained, the investigator of the conducting medical institution where the adverse event occurred shall make an additional report to the head of each conducting medical institution as soon as possible, and the study coordinating physician and the investigator. Report to the investigational device provider. The handling of the additional information shall be in accordance with the procedures 1) to 5) above, and shall be reported to PMDA as necessary.

**Case handling**

As a general rule, for registered cases, the investigator and the person in charge of statistical analysis will discuss and decide how to handle the cases. The clinical trial coordinator and the person in charge of statistical analysis will also decide on the handling of cases in the event of a new problem after consultation.

**Data handling**

As a general rule, the handling of data at the time of data aggregation / analysis shall be as shown below. If any doubt arises, the person in charge of statistical analysis and the investigator will make a decision before fixing the data in consultation.

Missing values are not complemented.

**Analysis of subject background**

Calculate the distribution and summary statistics of subject background data in each analysis target population. For nominal variables, the frequency and proportion of categories are shown. For continuous variables, calculate summary statistics.

**Safety and efficacy analysis**

Visual acuity (corrected decimal visual acuity converted to logMAR visual acuity is used to analyze the amount of change from baseline at week 12. A linear mixed-effects model is used as the statistical method, and the significance level of the hypothesis test is 5% on both sides. And the confidence interval is calculated as 95% confidence interval on both sides). If model analysis cannot be performed, only summary statistics are calculated. The detailed analysis method will be described in the statistical analysis plan.

Analysis of secondary efficacy endpoints included visual acuity (corrected decimal visual acuity converted to logMAR visual acuity and ETDRS visual acuity), static visual field test (HFA) 10-2 program and Estherman test (100 points). Perform statistical analysis. Multiplicity is not adjusted in the analysis of the secondary efficacy endpoint. A linear mixed-effects model is used as the statistical method, the significance level of the hypothesis test is 5% on both sides, and the confidence interval is 95% on both sides. If model analysis cannot be performed, only summary statistics are calculated. The detailed analysis method will be described in the statistical analysis plan.

For safety analysis, adverse events are aggregated, the number and proportion of cases of occurrence are aggregated, and a list is created for the presence or absence and severity of occurrence. In addition, the exact two-sided 95% confidence interval for the binomial distribution for the presence or absence of expression is calculated, and an appropriate significant difference test is performed as necessary.

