# 0. Overview

| Title | A study on the safety and efficacy of transcutaneous electrical stimulation for non-arteritic ischemic optic neuropathy (Phase II / III study) |
| --- | --- |
| Purpose | To confirm the safety and efficacy of transcutaneous electrical stimulation using skin electrodes for patients with non-arteritic ischemic optic neuropathy for visual function after treatment. |
| Design | prospective, non-randomized, open-label, uncontrolled multicenter trial |
| Phase | Ⅱ/Ⅲ |
| Device | 1. Overview   This device is that a skin electrode for electrical stimulation is attached to the center of the forehead and the skin on the lower eyelid ear side of the target eye to give constant electrical stimulation under various conditions to treat retinal and optic nerve diseases.  Constitution  　It consists of an "electrical stimulator", a "skin electrode" and an "electrode connection cable" that connects them.   1. Specification 2. Electrical stimulation device  - Current 0～3 mA   ・Time 0～10 msec×2 biphasic  ・Inverval 50 msec   1. Skin electrode　（Sekisui Kasei Co.Ltd.）   ・Size　　　　19×38 mm  ・Element　　　Ag/Agcl  ・Base material　　　　　Non-woven fabric  ・Gel 　　　　Conductive adhesive gel   1. Capacitance   AC adapter rating (input)　AC 100 V　50/60 Hz　30 VA  AC adapter rating (output)　DC 5 V　4 A   1. Weight：700 g、Size： 225×165×40 mm |
| Inclusion Criteria | 1. Clinically diagnosed with NAION and age ≥20 years and ≤80 years  2. NAION patients who were determined to have fixed symptoms more than 6 months after the onset  3. Decimal visual acuity from hand motion to 0.7  4. Patients who provided signed consent with sufficient understanding after receiving an explanation of the responsibilities of participating in this trial  5. Regular hospital visits every 2 weeks for 12 weeks |

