| Methods | This clinical trial consists of a pre-observation period and a clinical trial period.  The clinical trial period will be 12 weeks, and transdermal electrical stimulation treatment using skin electrodes will be performed 6 times every 2 weeks. The stimulation conditions during this treatment are as follows.  ＜Stimulation conditions＞   - Current strength：1.0 mA - Pulse duration：10 ms/phase - Frequency：20 Hz - Time：30minutes |
| Discontinuance criteria | 1) When the subject offers to decline participation in the clinical trial or withdraws consent.  2) When the subject is found to be ineligible for the subject after enrollment in the clinical trial.  3) When it is difficult to continue the clinical trial due to exacerbation of complications.  4) When it is difficult to continue the clinical trial due to adverse events.  5) If pregnancy is found.  6) If the entire clinical trial is discontinued.  7) When other serious violations of the clinical trial protocol are found.  8) When the necessity of discontinuation is recognized at the discretion of the investigator or the investigator. |
| Target number | 5 eyes of 5 patients |
| Trial period | Implementation period： 15 months （April 1. 2019～June 30. 2020）  Registration period： 12 months 　（April 1. 2019～March 31. 2020） |
| Facilities number | 3 |
| Ethics | Informed consent was obtained from all the patients for the electrical stimulation and other examinations. Written informed consent was obtained from all patients before enrollment. The study procedures conformed to the tenets of the Declaration of Helsinki. |
| The Institutional Review Boards | Prior to conducting this clinical trial, the Institutional Review Boards of the conducting medical institution will review the ethical, scientific and medical validity of this clinical trial. This clinical trial will be conducted after obtaining the approval of the Institutional Review Boards.  The Institutional Review Boards will continuously review whether the study is being conducted properly at least once a year. |

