**Implementation schedule and procedure**

The schedule for observation, inspection, and evaluation is shown in the table below. The investigator or the investigator will carry out observations and examinations according to the schedule. Items that can be carried out by the investigator, such as subject background surveys and clinical tests, may be carried out by the investigator under the control of the investigator. (See the schedule below)

|  | **Screening** | **0 week** | **2 weeks** | **4 weeks** | **6 weeks** | **8 weeks** | **10 weeks** | **12 weeks** | **Drop out** |
| --- | --- | --- | --- | --- | --- | --- | --- | --- | --- |
|  | Visit 1-2 | Visit 3 | Visit 4 | Visit 5 | Visit 6 | Visit 7 | Visit 8 | Visit 9 |  |
| IC | **○** |  |  |  |  |  |  |  |  |
| TdES |  | **①** | **②** | **③** | **④** | **⑤** | **⑥** |  |  |
| Blood pressure | **○** |  |  |  |  |  |  |  |  |
| Blood sampling | **○** |  |  |  |  |  |  |  |  |
| contrast-enhanced MRI | **○** |  |  |  |  |  |  |  |  |
| logMAR VA | **○** | **○** | **○** | **○** | **○** | **○** | **○** | **○** | **○** |
| ETDRS VA | **○** | **○** |  |  |  |  |  | **○** | **○** |
| HFA | **○** |  |  |  |  |  |  | **○** | **○** |
| Slit | **○** |  |  | **○** |  |  |  | **○** | **○** |
| IOP / fds | **○** |  |  | **○** |  |  |  | **○** | **○** |
| AEs | **○** | | | | | | | | |

**Abbreviations:** IC, informed consent; TdES, transdermal electrical stimulation; VA, visual acuity; HFA, Humphrey field analyzer; Slit, slit lamp examination; IOP, intraocular pressure; fds, fundus examination; AE, adverse event.

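### If the mixed model cannot be fitted, the protocol's fallback drops the confidence interval and the test, although a paired t-interval is available with five patients

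*Protocol*

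**What the plan says.** The Overview describes a "prospective, non-randomized, open-label, uncontrolled multicenter trial" with a target of "5 eyes of 5 patients". With no control group, efficacy rests on within-patient change.

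Under *Safety and efficacy analysis*, the primary analysis is to "analyze the amount of change from baseline at week 12" in logMAR acuity: "A linear mixed-effects model is used as the statistical method, and the significance level of the hypothesis test is 5% on both sides", with a two-sided 95% interval. The secondary paragraph repeats this for logMAR, ETDRS and the two Humphrey field measures (10-2 mean deviation and Esterman score): "A linear mixed-effects model is used as the statistical method, the significance level of the hypothesis test is 5% on both sides", again with a 95% interval. Each paragraph carries the same fallback: "If model analysis cannot be performed, only summary statistics are calculated". Each leaves the detailed method to the SAP.

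The table under *Implementation schedule and procedure* gives these times, apart from the drop-out visit:

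- logMAR: screening, week 0 and every two weeks to week 12.
- ETDRS: screening, week 0 and week 12.
- Visual field: screening and week 12.

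The Overview defines the secondary endpoints as changes. *Data handling* rules out imputation.

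**The concern.** The choice of covariance, random effects and degrees of freedom may properly wait for the SAP. The fallback does not wait: the protocol fixes it, and the word *only*, coming after a sentence that promises a test and an interval, excludes both. An SAP that supplied an interval after a failed fit would contradict the protocol.

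Three secondary endpoints have a single post-treatment value and are defined as changes, so the most literal mixed model for them is one that cannot be estimated. With five patients, a richer model for the repeated logMAR values may also fail. The planned inference would then be lost because one method failed, not because the data cannot support an interval.

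**Working it through.** The protocol gives no effect size, SD or power, so there is no stated figure to reproduce. The inputs are n = 5 with one eye each, the schedule, and the fallback sentence. Every variance and correlation below is an assumption.

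**1. One change score per patient.** Let d_i = δ + b_i + e_i, with b_i the patient effect and e_i the residual. Then Var(d_i) = σ_b² + σ_e², and only the sum enters the likelihood. In a numerical check with five changes, the REML log-likelihood was 5.2428 for every split between the two components, and the fit stopped with a singular matrix. The model is not identifiable.

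**2. Raw pre-treatment and week-12 values.** Let y_ij = μ + τ·t_j + b_i + e_ij, with two values per patient (10 observations). The patient effect cancels in the difference, so the estimate of τ is the mean paired difference. Its standard error is √(2σ_e²/n), which is the paired standard error provided the estimated patient variance is above zero. In an example fit the estimate was −0.0670 with SE 0.0598, equal to the paired analysis. In 200 repeats (assumed SDs 0.3 between patients, 0.1 residual) none was singular, and 199 converged with the paired SE.

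**3. Primary logMAR endpoint, five patients.**

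- Random intercept, visit as a factor: 1 non-convergence in 500 simulated trials.
- Random intercept and slope: 39 of 200 did not converge and 85 of 200 were singular (assumed SD 0.3 logMAR).
- Unstructured covariance: 7 × 8 / 2 = 28 parameters for weeks 0 to 12, or 6 × 7 / 2 = 21 for the six post-baseline visits, from five patients.

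Whether the model fails therefore depends on the specification.

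**4. What remains available after failure.** The paired interval is mean change ± t(0.975, n−1) × SD/√n.

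- n = 5: 2.776/√5 = 1.24, so ± 1.24 SD on 4 df.
- n = 4: 3.182/√4 = 1.59, so ± 1.59 SD on 3 df.

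Power at two-sided 5% with n = 5 is 40% for a mean change of 1.0 SD and reaches 80% only at 1.68 SD. A signed-rank test is no substitute: its smallest two-sided p with n = 5 is 2/2⁵ = 0.0625.

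**5. Error rate when a random-intercept model does fit (illustrative).** Week 12 versus week 0, seven visits, no true change, 24 df, 40,000 trials per setting:

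| Assumed truth | Type I error |
|---|---|
| Parallel courses, independent errors | about 5% |
| Change SD 0.03, residual SD 0.10 | 5.2% |
| Change SD 0.05, residual SD 0.10 | 6.1% |
| Change SD 0.10, residual SD 0.10 | 8.7% |
| Change SD 0.10, residual SD 0.05 | about 16% |
| AR(1) errors, 0.3 / 0.6 / 0.8 | 6.5% / 10.3% / 14.3% |

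The paired t-test on 4 df stayed at 4.9% to 5.0% in the four settings where it was run alongside (change SD 0.10 with either residual SD, and AR(1) 0.6 and 0.8).

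**The case against.** The strongest reply is that nothing need fail. The protocol does not say that the secondary model's response is the change score. A raw-value model is a standard way to estimate change, and it fits with five patients. For logMAR the SAP can choose a structure that converges and suitable degrees of freedom. In a five-patient, open-label, uncontrolled study, descriptive reporting after a failed fit is also transparent and adds no false positives. Given the power shown above, little is lost. If the mean, SD and number of changes are among the summaries, a reader could work out the interval.

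Most of this stands, and it rules out two stronger readings. A reader might infer that the mixed model cannot be fitted to ETDRS and the visual field. The schedule does not support that, because each has at least one pre-treatment value and a week-12 value. A reader might also infer that the primary p-value will be too optimistic. That rests on covariance, degrees of freedom and variances that the protocol does not state, and under parallel courses with independent errors the test holds its level.

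What the reply does not answer is the fallback itself. An interval worked out afterwards is not a planned one, and the protocol does not say that the summaries will be of changes. The SAP cannot add an interval without departing from the protocol.

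**Conclusion.** The fallback is badly fixed: when the model fails, it discards the interval and test although small-sample inference is available from the same data. This follows from the protocol's wording and from the t-interval, which needs at least two patients with both values, some spread in the changes, and roughly normal changes. How likely the rule is to apply is not known. For ETDRS, mean deviation and Esterman it applies if change scores are modelled with a patient random effect, and not if raw values are modelled. For primary logMAR it depends on the SAP.

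The simulated convergence and error rates are illustrations under assumed values and carry no weight beyond that. Severity is minor to moderate, not must-fix.

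**What to change.** 1. In both places under *Safety and efficacy analysis*, replace the fallback. Suggested wording: if the mixed model cannot be fitted, report the mean paired change from baseline to week 12 with its two-sided 95% t-interval on n − 1 degrees of freedom, where n is the number of patients with both values.
2. State that ETDRS acuity, 10-2 mean deviation and Esterman score are analysed by this paired change, or equivalently by a mixed model on the raw baseline and week-12 values with n − 1 degrees of freedom. For the visual field the baseline is the screening value, the only one scheduled before treatment.
3. Do not name a signed-rank test as the fallback.
4. For primary logMAR, keep the mixed model and report the paired t-interval beside it as a sensitivity analysis. Making the paired test primary would be a trade-off, because it discards weeks 2 to 10 and any patient without a week-12 value.

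The cost is wording in the protocol and matching text in the SAP. The interval will be wide: at equal standard error, 4 df instead of 24 widens it by about 35% (2.776/2.064 = 1.345), and one missing week-12 value raises the half-width from 1.24 to 1.59 SD.

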**Effectiveness and Safety Evaluation Committee**

In this clinical trial, an efficacy and safety evaluation committee will be set up. The Efficacy and Safety Assessment Committee was established as an independent body of the investigator and consists of members of her three or more experts who are independent of the study. The Efficacy Safety Evaluation Committee conducts safety monitoring, such as comparison of adverse event incidence rates in study treatment and detailed examination of serious adverse events, as necessary, for the purpose of ensuring the safety of subjects. conduct. Occasionally, based on the results, in order to reduce the risk of adverse events, it may be recommended to change the clinical trial design such as changes in the inclusion criteria, or it may be decided whether or not the clinical trial can be continued. For details, refer to "Standard Business Procedures for Effectiveness and Safety Evaluation Committee".

**Final analysis**

After the follow-up period ends, data will be obtained and the case will be fixed before analysis. The person in charge of statistical analysis compiles an "analysis report" and submits it to the investigator and investigator. The clinical trial coordinator summarizes the contents of the analysis report, prepares a "summary report" that summarizes the conclusions, problems, interpretation and consideration of the results, future policies, etc. of the entire clinical trial from a clinical perspective, and is responsible for the clinical trial. Obtain the approval of a doctor.

